**Table d31e757:** 

**ML session**	**Title of Album(s)**	**Artist(s)**
1	Well-balanced	Oliver Shanti
2	AVWF–Classics I	AVWF®
3	QE2; Earth Moving	Mike Oldfield
4	Violine Volume I	AVWF®
5	The Beatles; The Beatles	Munich Symphonic Sound Orchestra; Classic Dream Orchestra
6	See session 1	
7	See session 4	
8	See session 5	
9	See session 3	
10	Guitar I	AVWF®
Participants will listen to a mix of music pieces of the specified album and artist for 60 min in each session. Frequency modulation increases with session number in the frequency-modulated researcher-selected music-listening (ML) condition.		

For persons with average hearing ability, the frequency modulation is typically not detectable according to the AVWF developer. We conducted a pilot study with a convenience sample of 10 healthy subjects (seven women, three men, all psychology students) in order to test whether participants would be able to guess correctly if they listened to frequency-modulated or unmodulated music. We randomly assigned participants to one of the two conditions (5 per group) and chose a composition of classic instrumental music that was self-composed by the AVWF developer for both conditions. Moreover, for the frequency-modulated music condition, we decided to apply a modulation stage that would be usually played during the sixth session (i.e., advanced modulation of frequencies compared to the first sessions). Participants listened to the respective music for a duration of 20 min in sitting position via headphones. Afterwards, they filled out a paper-pencil questionnaire asking them (a) to indicate whether the music they listened to was presumably frequency-modulated or unmodulated and (b) to estimate how confident they feel in their answer on a VAS ranging from 0 to 100%. One participant did not provide answers, leaving data from nine participants for evaluation. Three participants (33.3%) allocated to the frequency-modulated music made the correct guess with an average confidence level of 50.3%. It is notable that one of these three participants had visual impairments and reported extremely good hearing abilities. Moreover, three participants (33.3%) who were allocated to unmodulated music, guessed wrongly and reported having been listening to frequency-modulated music with an average confidence level of 43.0%. Furthermore, one participant (11.1%) reported correctly having listened to unmodulated music with a confidence level of 15.0% and two participants (22.2%) thought they listened to unmodulated music although they had been allocated to the frequency-modulated music, with an average confidence level of 42.5%. In summary, considering the 50% chance of guessing correctly and that those who did guess correctly were not overall confident in their estimation, we concluded from these results that there was no systematic identification of frequency-modulated music, confirming the notion that frequency modulation is typically undetectable.

#### Unmodulated Researcher-Selected Music

The same music pieces in identical sequence as in the frequency-modulated researcher-selected music condition (see Box 2) will be presented to participants. However, music pieces will not be frequency-modulated and will be presented via a music delivery system without modulating features.

#### Unmodulated Self-Selected Music

Participants will receive an email before their baseline appointment instructing them to compile 120 min of their favorite music, irrespective of genre or other musical characteristics (e.g., tempo, instrumental, vocal). Participants will be assured that their personal selection will not be judged in any way and that they should select songs or musical excerpts that they will be able to enjoy listening to for 60 min. Participants will also be advised to bring their compilation on a portable memory device in mp3 format at their baseline appointment, when the examiner will transfer the music onto the study server and onto the music-delivery system without modulating features for the subsequent 10 music-listening sessions. During the intervention period, the self-selected music will be played in shuffle mode in order to ensure variation across and within sessions. On every occasion, the current playlist will be recorded by the scientific co-worker for our internal records.

### Materials and Equipment

#### Music-Delivery Systems

Music will be presented via two different non-commercially available music-delivery systems [as described in (75)]. One of these will modulate the music via specific hardware components while the other will play music unaltered. Both systems consist of a computer with touch display and an amplifier built into a wooden case and equipped with Windows media player software. All participants will listen to their respective music via over-ear headphones (beyerdynamic, Heilbronn, Germany).

#### Pain Induction

The cold pressor test (CPT) is a safe, reliable, and frequently applied method to induce cold pain in experimental settings (107, 108). The CPT apparatus consists of a plastic bucket filled with crushed ice and water. A metal grid placed into the bucket holds the ice at the bottom of the bucket, and an electrical pump constantly circulates the water to maintain a constant temperature within the bucket. The target temperature is 1°C and is controlled by a thermometer. Participants are asked to immerse their dominant hand into the water up to their wrist without moving their hand or making a fist. Participants are instructed to keep their hand in the water for as long as they can stand it. In this study, participants will be facing a wall, and the examiner will turn away from the participant in order to eliminate confounding due to social desirability. When extracting their hand from the water, the participants will be asked to signal this verbally to the examiner. After a maximum duration of 3 min, participants will be asked to pull their hand out of the water in order to prevent any potential tissue damage. Moreover, participants do not know after which of the music-listening sessions they will be exposed to the CPT in order to avoid anticipation effects.

#### Outcome Measures

##### Course of Assessments

Table 1 reports the assessment schedule for measures of pain perception as well as for biological and subjective markers of stress. See Figure 2A for the protocol and timeline for baseline, post, and follow-up appointments and Figure 2B for the protocol and timeline for music-listening sessions 1, 3, 6, and 10. In accordance with our hypotheses regarding measures of pain perception and markers of stress, primary and secondary outcomes will be measured at baseline and post-intervention. Furthermore, to investigate the intermediate stability of potential benefits of the music-listening interventions, we have included a follow-up assessment 4 weeks after the post-assessment.

**Table 1 T1:** Assessment schedule for measures of pain perception and markers of stress.

**Measures**		**Online survey**	**BL**	**Intervention period**										**Post**	**FU**
				**M1**	**M2**	**M3**	**M4**	**M5**	**M6**	**M7**	**M8**	**M9**	**M10**		
Pain perception	Pain tolerance (seconds)		x	x		x			x				x	x	x
	Perceived pain intensity^a^ (VAS)		x	x		x			x				x	x	x
Subjective stress	Momentary stress^b^ (VAS)		x	x	x	x	x	x	x	x	x	x	x	x	x
	Chronic Stress (SSCS)	x												x	x
	Stress reactivity (PSRS)	x												x	x
Biological stress markers	HRV^c^		x	x		x			x				x	x	x
	EDA^c^		x	x		x			x				x	x	x
	Hair cortisol		x												x

*The intervention period comprises 10 sessions of music listening (for a duration of 60 min each) scheduled within 3 consecutive weeks. Perceived pain will be induced via the cold pressor test (CPT) at baseline (BL), music-listening sessions (M) 1, 3, 6, and 10 (after music listening, respectively), at post, and at follow-up (FU). Music-listening sessions 2, 4, 5, 7, 8, and 9 comprise music listening only and no subsequent pain induction*.

a *Perceived pain intensity will be assessed pre- and post-CPT*.

b *Momentary stress will be assessed pre- and post-music listening and pre- and post-CPT*.

c *HRV and EDA will be derived from resting state (=10 min) at baseline, post, and follow-up; in addition, HRV and EDA will be measured continuously throughout music-listening sessions 1, 3, 6, and 10*.

*EDA, electrodermal activity; HRV, heart rate variability; PSRS, Perceived Stress Reactivity Scale; SSCS, Screening Scale for Chronic Stress; VAS, visual analog scale*.

The intervention period encompasses 10 sessions of music listening, each for a duration of 60 min, within 3 consecutive weeks. Music-listening sessions 1, 3, 6, and 10 will also include assessments of perceived pain in response to cold pain (induced via the CPT after music listening) and continuous measurements of biomarkers of the ANS as well as measurements of momentary subjective stress before and after music listening, as well as before and after the CPT. Furthermore, we will assess a range of tertiary variables during the course of the study (e.g., music-induced emotions, mood). The detailed assessment schedule including all measured variables (primary, secondary, tertiary) is reported in the Supplementary Tables 1, 2.

##### Primary Outcomes

Pain tolerance and perceived pain intensity: Pain tolerance will be operationalized via time in seconds elapsed from immersion until extraction of the hand during the CPT. It will be recorded by the examiner using a stopwatch. Perceived pain intensity will be measured before and after the CPT via paper-and-pencil visual analog scales (VAS). Participants will be provided with a piece of paper containing the sentence “I am in pain” and a 10 cm line ranging from 0 to 100. They will be instructed to mark the line accordingly (0 = no pain, 100 = maximal pain). Additionally, after the CPT, participants will be asked to report how painful they perceived the CPT to be by responding to the sentence “The test was painful” and again marking a VAS corresponding to their experience (0 = not at all painful, 100 = maximally painful). Measures of pain perception will be assessed at baseline, post, and follow-up as well as after music listening in sessions 1, 3, 6 and 10 (see Table 1 and Figure 2).

##### Secondary Outcomes

Since stress is a multidimensional phenomenon, we consider biological (autonomic, endocrine) as well as subjective indicators that operationalize different aspects and time-varying characteristics of stress as our secondary outcomes (109).

##### Autonomic and Endocrine Stress Markers

###### Heart Rate Variability

We will record an electrocardiogram (ECG) at a sampling rate of 256 Hz for the analysis of heart rate variability as an indicator of ANS activity using Equivital EQ02 Life Monitors and Equivital Life Shirts (Hidalgo Limited, Cambridge, UK). Time domain (e.g., square root of the mean squared differences between successive RR intervals, RMSSD; percentage of successive RR intervals that differ by more than 50 ms, pNN50) as well as frequency-domain (e.g., high-frequency band, HF; low- to high-frequency ratio, LF/HF) indices (110) will be calculated. At baseline, post, and follow-up, ECG recordings will take place at rest for 10 min while watching a video featuring landscapes (111) with the sound turned off. At the same appointments, ECG will be additionally recorded continuously (i.e., including pain induction). In music-listening sessions 1, 3, 6, and 10, ECG will be recorded constantly throughout the whole session (i.e., including music listening and pain induction).

###### Electrodermal Activity

Electrodermal activity (EDA) will be recorded at a sampling rate of 16 Hz using Equivital EQ02 Life Monitors and corresponding EQ-ACC-034 EDA sensors (Hidalgo Limited, Cambridge, UK). EDA will be derived from the intermediate phalanx of the middle and index finger of the non-dominant hand using pre-gelled Biopac EL507 electrodes with Ag/AgCl contacts (Biopac Systems Inc., Goleta, CA, USA). Recording will take place analogously to ECG recordings.

###### Hair Cortisol

Cortisol is the main effector hormone of the hypothalamic-pituitary adrenal axis, an important stress-sensitive system besides the ANS. The secretion of cortisol is increased upon exposure to environmental stressful situations and accumulates in hair, reflecting a measure of chronic stress exposure (112). Hair samples for the subsequent analysis of hair cortisol will be taken at baseline and follow-up assessment. Three strands of hair will be taken scalp-near from the posterior vertex region. The most scalp-near 1 cm of hair will be analyzed as this represents cortisol secretion in approximately the last month and thus gives insight into each individual's cumulative stress exposure over the month before sampling. In the context of this study, we will thus be able to assess chronic biological stress in the 4 weeks before baseline and in the 4 weeks before follow-up (reflecting the timeframe between the post-measurement and follow-up assessment).

##### Subjective Stress Measures

###### Subjective Momentary Stress

We will measure momentary subjective stress via VAS (paper-and-pencil) before and after music listening in all 10 music-listening sessions and before and after conducting the CPT (i.e., at baseline, music-listening sessions 1, 3, 6, 10, post, and follow-up). On each occasion, participants will be asked to respond to the sentence “I am feeling stressed” using a VAS ranging from 0 (not stressed at all) to 100 (maximally stressed).

###### Chronic Stress

We will use the Screening Scale for Chronic Stress (SSCS) comprising 12 items of the Trier Inventory of Chronic Stress (TICS) (113) at baseline, post, and follow-up assessment to measure subjective chronic stress. We have adjusted the reference period in the instructions of the SSCS from 4 weeks to 1 week so that baseline and post-assessment will not overlap. The TICS encompasses 57 items on six subscales (work overload, worries, social stress, lack of social recognition, work discontent, intrusive memories) and will be used at baseline, too.

###### Stress Reactivity

Stress reactivity will be measured by the German version of the Perceived Stress Reactivity Scale (PSRS) (114), administered at baseline, post, and follow-up assessment. The PSRS consists of five subscales (Prolonged Reactivity, Reactivity to Work Overload, Reactivity to Social Conflicts, Reactivity to Failure, Reactivity to Social Evaluation) which can be combined into one overall scale.

##### Tertiary Variables

Tertiary variables will be assessed throughout the study. These may serve as outcome, control, moderator and/or mediator variables in exploratory analyses related to the study. The assessment schedule for tertiary variables is displayed in the Supplementary Tables 1, 2.

In each music-listening session, momentary mood [short scale of the Multidimensional Mood Questionnaire, MDMQ-short (115)] will be assessed directly before and after music listening. Additionally, based on previous literature investigating the impact of music on measures of pain perception and stress, we developed a questionnaire assessing music-related perceptions concerning the respective music that was listened to. The questionnaire will be provided after music listening in each session. It includes questions on music-induced emotions, perceived valence and arousal of the music, music-induced memories, and is also thought to control for mind-wandering or sleeping during the music-listening sessions (see questionnaire 1 in online Supplementary Material). Furthermore, musical engagement between sessions will be assessed (see questionnaire 2 in online Supplementary Material) as a potential control variable.

At baseline, post, and follow-up assessments, the following additional variables will be assessed via questionnaires: emotion regulation strategies [Emotion Regulation Questionnaire, ERQ (116)], fatigue [Multidimensional Fatigue Inventory, MFI-20 (117)], sleep quality [Pittsburgh Sleep Quality Index, PSQI (118)], and depressive symptoms [Beck Depression Inventory-II, BDI-II (101)]. Moreover, at baseline only, cognitive style of music listening (Music-Empathizing-Music-Systemizing (ME-MS) Inventory), music preferences [revised version of the Music Preference Questionnaire, MPQ (119)], personality traits [openness to experience, conscientiousness, extraversion, agreeableness, neuroticism, Big Five Inventory-10 (120)], perceived social support [subscale of the Berlin Social Support Scales, BSSS (121)], and menstrual cycle phase (self-report) will be assessed.

For the purpose of monitoring the participants during the intervention period, they will receive paper-and-pencil questionnaires with open-ended questions at the end of music-listening sessions 1, 3, 6, and 10. This will enable them to report whether they felt any disturbances associated with the music-listening session and whether they had any specific thoughts during the CPT in order to control for cognitive pain-coping strategies.

At the end of the post-assessment, participants will receive a paper-and-pencil post-monitoring questionnaire, asking them to indicate which condition (i.e., frequency-modulated or unmodulated music) they believe they were assigned to and how confident they are in this belief. Moreover, participants will be asked whether they perceived increased self-awareness due to study participation, whether any positive or negative changes in well-being, mood, or general health occurred during the course of the intervention, and to state how compatible study participation was with their individual schedules. At the follow-up assessment, final post-monitoring and control questions regarding musical engagement, previous familiarity with and use of music-listening interventions and study conformity will be assessed.

### Sample Size Determination

Previous investigations employing a comparable design are lacking and we consider the current study a pilot trial in order to yield sufficient precision for a sample size calculation in a subsequent full trial. Therefore, following the recommendations mentioned in (122, 123) and (124), we decided to test 30 participants in each group. A power analysis using G^*^Power 3 (125) suggested that this sample size will be sufficient to achieve a medium effect (*f* = 0.25) in a repeated-measures analysis of variance (α = 0.05, power (1-β) = 0.80) with condition as the between-subject factor (frequency-modulated researcher-selected vs. unmodulated researcher-selected vs. self-selected) and time (baseline vs. post) as the within-subject factor. In the case of dropouts, we will continue recruitment and repeat the randomization procedure until at least a number of 30 participants is collected in each group. Thus, the final number of participants in each group might slightly differ.

### Statistical Analysis

Repeated-measures analyses of variance will be conducted to test our main hypotheses 1 and 2. Mediation hypotheses will be tested with continuous time modeling procedures. *P*-values of ≤ 0.05 will be considered statistically significant. Analyses for comparisons between the researcher-selected frequency-modulated and self-selected unmodulated music conditions will be conducted in a two-sided manner. Any further exploratory analyses will be specified in future publications. We will perform both per-protocol and intention-to-treat analyses. Missing data will be imputed in accordance with (126).

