Listening to researcher-selected frequency-modulated music and self-selected unmodulated music will result in stronger increases in pain tolerance and stronger decreases in perceived pain intensity from baseline to post-intervention compared to listening to researcher-selected unmodulated music.Stronger decreases in biological and subjective markers of stress from baseline to post-intervention are expected in the researcher-selected frequency-modulated music and self-selected unmodulated music-listening conditions than in the researcher-selected unmodulated music-listening condition.Since there is no previous literature indicating a superiority of researcher-selected frequency-modulated or self-selected unmodulated music, we will test these comparisons in a two-sided manner.Changes in pain tolerance and perceived pain intensity will be mediated by changes in biomarkers of the ANS and subjective stress.

In addition to these main hypotheses, we will examine whether reductions in measures of pain perception and markers of stress persist until the follow-up assessment (4 weeks after the post-assessment) aiming at investigating the potential intermediate stability of the effects.

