**Figure 1 F1:**
[figure not shown]
Study flow diagram.

Overall, 90 participants (30 participants per intervention condition) will attend a baseline assessment, followed by 10 sessions of music listening conducted within 3 consecutive weeks. Finally, post and follow-up assessments will be conducted. We do not anticipate protocol modifications. Nevertheless, if any trial modifications should be considered necessary, all changes in design, measures, or eligibility criteria will be recorded in the online protocol registration entry and will be included in the final manuscript for journal submission.

Following the study preparation phase (April–November 2016), recruitment and testing started in December 2016 in Marburg, Germany. Due to the move of our lab from Marburg, Germany, to Vienna, Austria, recruitment and testing needed to be paused as of January 2018 for 9 months. Testing continued in October 2018 and is presumed to be accomplished in December 2022.

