### Randomization

We will use a block randomization stratified by gender using the blockrand package (103) and the statistical software R, version 3.4.2 (104). Block lengths will vary randomly between 3, 6, and 9. The randomization procedure will be performed by an independent researcher unrelated to the study. The resulting 90 computer-generated notes stating participant gender and experimental condition will be placed into separately sealed envelopes and stored in a locked cabinet. Upon inclusion of a new participant, the project coordinator will draw an envelope containing the note with the respective condition to which the included participant will be assigned. This information will be shared with the scientific co-worker who will be in charge of setting the music-delivery systems (see below) during the course of the intervention period, but not with the experimenter.

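### The planned baseline-to-post repeated-measures ANOVA for hypotheses 1 and 2 is valid but amounts to comparing change scores; adjusting for the baseline already collected would be more precise

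*Protocol article*

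**What the plan says.** The Statistical Analysis section of the protocol article names the test for the first two main hypotheses: "Repeated-measures analyses of variance will be conducted to test our main hypotheses 1 and 2". It lists neither factors nor covariates.

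The factors appear in Sample Size Determination, where the power calculation takes condition "as the between-subject factor (frequency-modulated researcher-selected vs. unmodulated researcher-selected vs. self-selected) and time (baseline vs. post) as the within-subject factor". The Study Aims and Hypotheses section words the first hypothesis in the same terms, for example "stronger decreases in perceived pain intensity from baseline to post-intervention", and compares that change between arms. Read together, these make the test of interest the condition-by-time interaction over two time points.

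Three other facts bear on the choice of model:

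- **Randomisation:** "We will use a block randomization stratified by gender using the blockrand package". Gender is the only stratum named.
- **Site:** "Due to the move of our lab from Marburg, Germany, to Vienna, Austria, recruitment and testing needed to be paused". Testing ran in Marburg until December 2017 and resumed in Vienna in October 2018, so each participant's site is known.
- **Timing of baseline:** under Recruitment, Screening, and Consent, allocation happens before the baseline appointment. Under Study Setting and Procedure, participants in the self-selected arm compile their music before that appointment.

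**The concern.** With only two time points, the interaction test uses the baseline in one fixed way: it subtracts it. That is the most precise use only when baseline and post values are almost perfectly correlated. At any lower correlation, subtraction adds baseline noise to the contrast, and estimating the slope removes some of that noise at no cost in data.

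This matters because precision is scarce here. There are 30 participants per arm, each attending 13 appointments. Sample Size Determination gives the purpose of the pilot as supplying enough precision to size a later trial, and the Discussion says its effect sizes will inform such trials. The primary outcomes are measured at baseline in any case, so the gain needs no new measurement.

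**Working it through.** **Inputs from the article.** Three arms of 30 (N = 90), two time levels, alpha 0.05, power 0.80, f = 0.25. Pain tolerance is capped at 3 min (180 s).

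**Assumptions.** The article gives neither rho nor any SD. I use rho from 0.3 to 0.9 for comparing the methods, equal variances at baseline and post, and, for one illustration, a pairwise difference of 0.5 baseline SD.

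**Step 1. The article's own figure.** Neither rho nor the G*Power option is stated, so 0.80 at N = 90 cannot be matched uniquely. For the interaction, lambda = f² × N × 2/(1 − rho), with 2 and 87 degrees of freedom:

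- rho 0: lambda = 0.0625 × 180 = 11.25, power 0.85
- rho 0.3: lambda = 11.25/0.7 = 16.07, power 0.95
- rho 0.5: lambda = 11.25/0.5 = 22.5, power 0.99

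On this option 90 participants do suffice for f = 0.25, as the article says. Other G*Power options give less: 0.67 for the between-condition effect at rho 0.5, and 0.54 under the Cohen-style definition of f.

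**Step 2. The identity.** On one simulated data set, the interaction F and the one-way F on change scores were both 0.32896. The identity concerns the interaction, not the main effect of condition.

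**Step 3. Relative precision.** With outcome variance s² at each time:

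- change-score variance = 2s²(1 − rho)
- ANCOVA residual variance = s²(1 − rho²)
- ratio = (1 − rho²)/[2(1 − rho)] = (1 + rho)/2

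The last column takes an effect that the repeated-measures ANOVA detects with power 0.80 at N = 90 (lambda = 9.97). It divides lambda by the ratio and allows three covariate degrees of freedom, with no extra explained variance from gender or site.

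| rho (assumed) | Variance ratio | 30 per arm is worth (30/ratio) | ANCOVA power |
|---|---|---|---|
| 0.3 | 0.65 | 46.2 | 0.94 |
| 0.5 | 0.75 | 40.0 | 0.90 |
| 0.7 | 0.85 | 35.3 | 0.86 |
| 0.8 | 0.90 | 33.3 | 0.84 |
| 0.9 | 0.95 | 31.6 | 0.82 |

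**Step 4. One pair of arms.** For an assumed 0.5 SD difference, 30 against 30, two-sided 5%, non-central t, power rises from 0.48 to 0.59 at rho 0.5 and from 0.69 to 0.76 at rho 0.7.

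**Step 5. Simulation (3,000 runs per setting).** With baseline, gender and site in the model and no real gender or site effect, the variance ratios were 0.66, 0.77, 0.87, 0.92 and 0.98 at rho 0.3, 0.5, 0.7, 0.8 and 0.9. Type I error stayed between 0.041 and 0.056 for all models.

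**Step 6. The 180 s cap.** With assumed lognormal tolerance times cut at 180 s, the ratio was 0.80 at rho 0.5, 0.95 at rho 0.8 and about 1.00 at rho 0.9. The gain for tolerance is smaller and can vanish.

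**Step 7. Gender and site.** Both are constant within a person, so an additive difference already cancels in a change score. In ANCOVA they help only if they predict the post value beyond baseline. With assumed gender and site effects in the simulation, adding the two terms to baseline moved the ratio only from 0.688 to 0.668 at rho 0.3 and from 0.778 to 0.767 at rho 0.5. Nearly all the gain comes from baseline.

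**Step 8. If preparing music shifts baseline in the self-selected arm by an amount D.** With equal variances the ANCOVA slope is about rho.

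- Shift at baseline only: the change score is off by D, ANCOVA by about rho × D.
- Shift that persists to post: the change score is off by 0, ANCOVA by about (1 − rho) × D.

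Neither analysis is the safer one in both cases.

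**The case against.** The strongest reply is that nothing here is wrong. Repeated-measures ANOVA is a valid randomised comparison, it matches hypotheses worded as change, and it agrees with the power calculation. Covariates are ordinary content for an analysis plan that is not shown. The size of the gain rests on a correlation that the article does not give.

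Most of this stands, and it limits the point. A reader might infer that the planned test is biased, through regression to the mean or chance baseline imbalance. The documents do not support that: under randomisation these do not favour any arm in expectation, and chance imbalance is a cost in variance already counted in the ratio.

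A reader might also infer that leaving out gender and site is an error. The factor list comes from the power calculation, the Statistical Analysis section excludes nothing, and additive differences cancel in change scores. Site is not a stratum, and small blocks should keep the arms roughly balanced across the move.

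Nor does the 0.48 in Step 4 show an underpowered trial. It follows from an assumed effect, whereas the article's own f = 0.25 gives 0.85 or more for the interaction.

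What the reply does not remove is that the article itself names the test. That choice is fixed, and a more precise one is available from data already planned.

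**Conclusion.** The point holds as one of efficiency. For hypotheses 1 and 2 the stated test is a change-score comparison, and baseline adjustment would cut the variance of the arm contrasts by 35% at rho 0.3, 25% at 0.5, 15% at 0.7, 10% at 0.8 and 5% at 0.9. These figures assume equal variances at the two times and a correlation the article does not state. The identity and the algebra are certain; the benefit in this trial is not, and for capped pain tolerance it may be close to nil. The two-level reading rests on Sample Size Determination and the hypotheses, since the Statistical Analysis section does not repeat the time levels.

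**What to change.** In the Statistical Analysis section:

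- Make the primary model for hypotheses 1 and 2 an ANCOVA of the post value on condition, baseline value and gender (the randomisation stratum). Site may be added as an optional covariate, decided in advance.
- For hair cortisol, which is sampled only at baseline and follow-up, use the follow-up value as the response.
- Take the arm contrasts in hypotheses 1 and 2 from this model.
- Keep the repeated-measures ANOVA as a sensitivity analysis. A clear disagreement between the two in contrasts with the self-selected arm should prompt a look at whether baseline shifted after allocation.

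The cost is a few sentences and two or three covariate degrees of freedom out of 87. The remaining drawback is the one in Step 8: because baseline follows allocation, a shift in the self-selected arm would affect the two analyses differently, and the sensitivity analysis is there to show it. The change should be made before outcomes are examined by arm.
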